### Health economic outcomes

Participants will prospectively record in a patient diary the following:

• presenteeism (self-reported capacity to work or perform daily activities) [58-60]

• instances of absenteeism

• use of healthcare and community services

• out-of-pocket costs of community services

These data will be collected over three six-week time periods from: (i) discharge from acute care, (ii) the 6-week follow-up assessment, and (iii) the 6-month (26-week) follow-up assessment.

Presenteeism will be rated from 0% (unable to do usual work/activities) to 100% (fully functioning). Absenteeism is defined as days off work (including home, volunteer or carer duties) due to TKR. The use of healthcare (e.g. visits to medical practitioners, physiotherapists, hospitalisation) and community (e.g. meals on wheels) services will be recorded in terms of the type of service, date of use and number of hours/days. Costs of community services will be the out of pocket costs incurred by participants. The use of medication will be included as a health economic outcome and will be collected at the time of each follow-up assessment.

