**Methods/Design:**

In this multicentre randomised controlled trial, 600 patients undergoing primary TKR will be recruited at the orthopaedic pre-admission clinic of 10 large public and private hospitals in Australia. There will be no change to the medical or rehabilitative care usually provided while the participant is admitted to the orthopaedic ward. After TKR, but prior to discharge from the orthopaedic ward, participants will be randomised to either the novel rehabilitation strategy or usual rehabilitative care as provided by the hospital or recommended by the orthopaedic surgeon. Outcomes assessments will be conducted at baseline (pre-admission clinic) and at 6 weeks, 6 months and 12 months following randomisation. The primary outcomes will be self-reported knee pain and physical function. Secondary outcomes include quality of life and objective measures of physical performance. Health economic data (health sector and community service utilisation, loss of productivity) will be recorded prospectively by participants in a patient diary. This patient cohort will also be followed-up annually for five years for knee pain, physical function and the need or actual incidence of further joint replacement surgery.

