### Interventions

#### Novel rehabilitation strategy

Stage 1: Initial home exercise programme (usually Week 1 to 6 after randomisation)

Participants will be provided with a written home exercise programme on discharge from acute care (Additional file 1). The exercises will focus on maintaining and improving active knee flexion and extension range of motion. Participants will repeat the exercises 5 to 10 times per exercise, three times daily. Participants' progress, including adherence to the home exercise programme, walking ability and knee symptoms (e.g. pain, wound healing, range of motion, swelling), will be monitored weekly by a research physiotherapist, with clinic visits in the first one or two weeks and by telephone calls thereafter.

Stage 2: Outpatient exercise classes (usually Week 6 to 14 after randomisation)

Approximately five weeks after randomisation, the research physiotherapist will commence screening during the weekly telephone calls to assess eligibility to commence the classes: (i) surgical wound healed, (ii) full weight-bearing tolerated on the operated limb, (iii) ambulating independently outdoors for more than 50 m, and (iv) not requiring daily opioid-based analgesics for knee pain. Participants will join the outpatient exercise classes as they become eligible.

The classes will be circuit-based and supervised by a physiotherapist. The one hour classes will be conducted twice a week. Participants will be encouraged to attend the ongoing classes for eight weeks. Each class will consist of a short warm up and cool down component, progressive functional and strengthening exercises, and a 20-minute monitored aerobic exercise session on a stationary bicycle (Additional file 1). In order to standardise this programme across centres, minimal equipment will be used and supervising physiotherapists will receive prior training from research staff as well as a written manual of procedures. Participants will record the loads, repetitions and sets for to each functional and strengthening exercise they complete, and the duration and exertion (maximal heart rate or the Borg Rating of Perceived Exertion Scale [36]) for the aerobic exercise, in an exercise diary during the classes.

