#### Control group

Participants in the control group will receive the usual rehabilitation management as recommended by their orthopaedic surgeon or provided by the hospital, and can be delivered in the inpatient or outpatient setting. Findings from a previous Australian national survey demonstrate that rehabilitation will usually commence immediately after discharge from the orthopaedic ward, be completed within 6 to 8 weeks after TKR and will be provided on an individual basis by a physiotherapist in the outpatient setting [30]. Rehabilitation received by the control group will be documented in the patient diary.

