### Health economic analysis

The economic evaluation will consist of a trial-based cost-utility analysis to assess the incremental cost per quality-of life-year (QALY) of the novel rehabilitation strategy compared to usual care. The primary analysis will be conducted from the perspective of the health sector. A secondary analysis will entail a societal perspective in which the additional costs (and cost savings) associated with use of community services, absenteeism and presenteeism will be factored in.

In the primary analysis, costs of healthcare services will be valued at standard rates published by the Australian Government: the Medical Benefits Scheme standard fees for medical services and procedures, the Pharmaceutical Benefits Scheme cost for medications and the Australian Refined Diagnosis Related Groups (AR-DRG) cost weights for hospital services. These will be factored with levels of utilisation to estimate the costs of healthcare use in participants.

In the secondary analysis, costs of community services will be based on the self-reported costs of participants. The costs of presenteeism will be estimated by the number of days worked weighted by the rate of presenteeism multiplied by the average wage rate for the relevant employment category. The costs of absenteeism will be estimated by the number of days absent from work multiplied by the average wage rate for the relevant employment category. For those engaged in unpaid work, the national average wage rate will be used. A separate set of cost-utility ratios will be presented in this secondary analysis incorporating the wider costs (and cost savings) to the community.

Health state utilities required to estimate QALY will be based on measures obtained from the SF-12 and transformed into health state utilities via the SF-6D algorithm [62]. Although no survival difference is expected between the two groups at 12 months, average quality of life over 12 months for each participant will be estimated and weighted by survival up to 12 months to determine, for each patient, a measure of QALY after TKR. Given likely variations in the 'usual care' across sites, separate incremental cost-utility ratios will be estimated for broad categories of usual care (inpatient or outpatient). Sensitivity analysis will test uncertainty in key parameters such as the selection of cost weights and statistical variation in quality of life scores.

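### The patient diary covers 18 of the 52 weeks over which QALYs are counted, and its second window closes about two weeks before the classes usually end

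*Protocol article*

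**What the plan says.** Under Health economic outcomes, the Protocol article lists presenteeism, absenteeism, healthcare and community service use, and out-of-pocket community costs as diary items ("Participants will prospectively record in a patient diary the following"). It fixes when the diary is kept: "These data will be collected over three six-week time periods from: (i) discharge from acute care, (ii) the 6-week follow-up assessment". A third window opens at 26 weeks. Medication is the exception and is collected at each follow-up assessment. The abstract likewise says that health economic data "will be recorded prospectively by participants in a patient diary".

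Under Health economic analysis, unit prices are combined with utilisation to give costs. On the effect side, "average quality of life over 12 months for each participant will be estimated and weighted by survival up to 12 months" to give each participant's QALYs. The section does not say how costs are obtained for weeks without a diary.

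The two programmes have different usual timing. In the novel arm the heading reads "Stage 2: Outpatient exercise classes (usually Week 6 to 14 after randomisation"), entry depends on meeting eligibility criteria, classes are held twice weekly, and "Participants will be encouraged to attend the ongoing classes for eight weeks". Control rehabilitation is expected to "be completed within 6 to 8 weeks after TKR" and is to be documented in the patient diary.

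**The concern.** A cost-utility ratio needs costs and effects over the same period. Here the effects run over a full year, while the diary observes about a third of it. What happens in the unobserved weeks has to be ignored or extrapolated.

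The cut-off at about week 12 also does not fall equally on the two arms. It lies after the usual end of control rehabilitation but before the usual end of the classes, which are the novel strategy's main added resource. The Discussion makes cost-effectiveness part of the primary aim and anticipates substantial savings, so the completeness of programme cost matters to a headline conclusion. The secondary societal analysis uses the same windows for community services, absenteeism and presenteeism.

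**Working it through.** **Inputs, all from the Protocol article**
- Diary: three windows of 6 weeks, starting at discharge, at the 6-week assessment and at the 26-week assessment (Health economic outcomes).
- QALY horizon: 12 months, taken as 52 weeks (Health economic analysis).
- Classes: 2 per week for 8 weeks, usually weeks 6 to 14 (Novel rehabilitation strategy). The dates agree: 6 + 8 = 14.
- Control rehabilitation: usual end 6 to 8 weeks after surgery (Control group).
- Assumption: surgery, randomisation and discharge are treated as one time point, because the gaps are not given. The close of the second window at about week 12 does not depend on this, since the 6-week assessment is timed from randomisation.

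The article states no coverage figure to reproduce.

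**Step 1: diary coverage**
- Covered: 3 × 6 = 18 weeks; 18/52 = 34.6%.
- Not covered: weeks 12-26 (14 weeks) and weeks 32-52 (20 weeks); 14 + 20 = 34 weeks; 34/52 = 65.4%.

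**Step 2: classes outside the second window**

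Scheduled classes: 2 × 8 = 16. For a start in week s (from 4 to 12), the block ends in week s + 8, so classes after week 12 = 2 × (s + 8 − 12) = 2 × (s − 4).

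| Start week | Classes after week 12 | Share of 16 |
|---|---|---|
| 5 (assumed) | 2 | 12.5% |
| 6 (usual timing) | 4 | 25% |
| 8 (assumed) | 8 | 50% |
| 10 (assumed) | 12 | 75% |

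Only the week-6 row rests on the article's own timing. The other rows show sensitivity to the start date.

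**Step 3: control rehabilitation**

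If it ends at week 6, 8 or 12, all of it lies inside the first two windows. If it ran to week 14, 12/14 = 86% would.

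**Step 4: what different rules would do with weeks 12-26**

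This step supposes that the classes are costed from the patient diary and start in week 6. The true remainder is then 4 classes, and the observed part is 2 × 6 = 12.

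| Rule for weeks 12-26 | Classes added | Total counted | Against 16 scheduled |
|---|---|---|---|
| Sum observed weeks only | 0 | 12 | 75% |
| Straight-line fall to none at week 26 | ½ × 2 × 14 = 14 | 26 | 163% |
| Carry the week 6-12 rate forward | 2 × 14 = 28 | 40 | 250% |

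The direction of the error depends on the rule, and none of the three recovers the 4 classes that remain on the usual schedule.

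**The case against.** The strongest reply is that the trial runs the classes itself and need not rely on the patient diary to count them. The article ties that diary explicitly to rehabilitation in the control arm. In the novel arm an exercise diary is filled in during each class, with no stop at week 12, and a research physiotherapist makes the early clinic visits and weekly calls. This stands: programme cost can be known in full. However, the exercise diary is described as a record of training content and exertion, and nothing links it to the costing.

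Second, the gap weeks are not wholly dark. Medication is collected at follow-up visits, musculoskeletal and cardiovascular adverse events leading to medical intervention are asked about at each follow-up, and registry linkage verifies hip and knee replacements. This also stands, although the article does not say that the last two feed the costing, and they do not cover every admission or visit.

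Third, windowed diaries spare participants effort, and an interpolation rule may well be in a full protocol or analysis plan that is not shown. The absence of that rule is therefore not held against the article. But the windows themselves are a stated data-collection choice. A later plan can choose how to fill 34 weeks, but it cannot recover prospective records that were never taken.

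Finally, 16 classes is the full schedule, which participants are only encouraged to attend. The control timing is a survey pattern, and the article itself expects usual care to vary by site.

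**Conclusion.** The mismatch is real: 18 of 52 weeks (35%) of diary observation are set against 12-month QALYs. In both arms, healthcare and community service use, absenteeism and presenteeism in weeks 12-26 and 32-52 are not captured by the diary. The second window also closes about two weeks before the usual end of the classes.

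A reader might infer more than the article supports:
- **That the novel arm's cost is under-counted and the ratio biased in its favour.** The article does not say that the classes are costed from the patient diary. The 25% loss applies only if they are, and the direction of bias depends on an unstated rule (12 to 40 classes counted against 16).
- **That half or three-quarters of the classes would be lost.** Those figures need assumed starts in week 8 or week 10.
- **That control rehabilitation is fully captured.** This holds for the usual pattern only; care after week 12 would fall outside the diary here too.
- **That the diary is the only source of utilisation data, or that it stops for good before the classes end.** Medication is collected elsewhere, and the diary pauses at about week 12 and resumes at week 26.

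The point is a cheap improvement to the health economic analysis. It does not touch the WOMAC primary outcomes.

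**What to change.** 1. State that the classes, early clinic visits and weekly calls are costed from class attendance, exercise-diary and research physiotherapist records for the whole programme. Exclude these contacts from the patient-diary count so that they are not costed twice.
2. At the existing 6- and 12-month assessments, add a short recall form on hospital stays, procedures, health-professional visits, community services and days off work since the last diary window. The recall periods would be about 14 weeks (weeks 12-26) and 20 weeks (weeks 32-52), so that costs span the same 52 weeks as the QALYs. The form goes to both arms, so it also picks up control rehabilitation that continues past week 12.
3. Presenteeism is a rating and does not lend itself to recall over months, so state how it is interpolated between windows.

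The cost is small: the class records already exist and the visits already take place. The downside is that recall over 14 to 20 weeks is less precise than a prospective diary. The form should be in place before participants reach the 6-month assessment, because the gap in the diary cannot be filled with prospective data later.

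### The secondary societal analysis values community services only at participants' out-of-pocket payments, so any share met by another payer is counted in neither economic analysis

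*Protocol article*

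**What the plan says.** The protocol article gives the valuation rule twice. Under Health economic outcomes: "Costs of community services will be the out of pocket costs incurred by participants". Under Health economic analysis: "In the secondary analysis, costs of community services will be based on the self-reported costs of participants".

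The analysis that uses these costs is described in the same section: "A secondary analysis will entail a societal perspective in which the additional costs (and cost savings) associated with use of community services, absenteeism and presenteeism" are to be included. Its purpose is also given: "A separate set of cost-utility ratios will be presented in this secondary analysis incorporating the wider costs (and cost savings) to the community".

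The main economic analysis has a different scope: "The primary analysis will be conducted from the perspective of the health sector". It values medical services, medications and hospital services at published government rates multiplied by utilisation. Community services are not among its cost items.

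On data collection, Health economic outcomes says that use of healthcare and community services "will be recorded in terms of the type of service, date of use and number of hours/days". Meals on wheels is the only community service named. The article does not say how it, or any other community service, is funded.

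**The concern.** What a participant pays is a cost from the participant's perspective. A societal perspective values the whole resource, regardless of who bears it. The two agree only when the participant bears the full cost. The article states a valuation rule that is narrower than the perspective it declares, so this is not a detail left to a fuller document.

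The rule also differs from the rest of the plan. Healthcare is valued as quantity times a standard rate, and absence from work as days times an average wage. Only community services are priced at what the participant happened to pay, so a service that is free to the participant counts as costing nothing.

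What is at stake is the community-service part of the societal incremental cost, and through it the secondary cost-utility ratio.

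**Working it through.** The article gives no community-service cost, participant share or expected use, so there is no figure to reproduce. The check has two parts.

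**1. Is the third-party share counted anywhere?**

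- Primary (health-sector) analysis: covers medical services and procedures, medications and hospital services. Community services are not included.
- Secondary (societal) analysis: adds community services, absenteeism and presenteeism, with community services at participants' self-reported payments.
- Planned sensitivity analysis: varies key parameters such as the choice of cost weights. Under the stated rule community services carry no cost weight, so there is none to vary.

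No section adds the part met by other payers.

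**2. What does the omission do to the between-arm difference?**

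Notation (all values below are assumptions):

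- c = full cost per use
- d = difference in mean uses per participant, novel strategy minus control
- s = share of full cost paid by the participant, first taken as equal in both arms

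Full societal difference = c × d. Planned estimate = s × c × d. Error = s × c × d − c × d = −(1 − s) × c × d.

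The understatement factor is (c × d) / (s × c × d) = 1/s:

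- s = 0.25: 1/0.25 = 4
- s = 0.50: 1/0.50 = 2
- s = 0.75: 1/0.75 = 1.33

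Illustration with c = 100 units:

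| s | Planned, d = −2 (full −200) | Error | Planned, d = +2 (full +200) | Error |
|---|---|---|---|---|
| 1.00 | −200 | 0 | +200 | 0 |
| 0.75 | −150 | +50 | +150 | −50 |
| 0.50 | −100 | +100 | +100 | −100 |
| 0.25 | −50 | +150 | +50 | −150 |
| 0.00 | 0 | +200 | 0 | −200 |

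With d = 0 and equal shares, both the full and the planned difference are 0.

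**Unequal shares.** In general the error is minus the between-arm difference in mean third-party-funded cost, and the 1/s factor no longer applies. For example, take c = 100, 2 uses per participant on the novel strategy at a share of 0.75, and 4 uses in control at a share of 0.25. The full difference is 100 × 2 − 100 × 4 = −200. The planned estimate is 0.75 × 200 − 0.25 × 400 = 150 − 100 = +50. The third-party-funded cost is 200 − 150 = 50 against 400 − 100 = 300, a difference of −250. The error, 50 − (−200) = +250, is minus that difference. The sign of the component has reversed.

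**Effect on the ratio.** The error enters the numerator alongside healthcare, absenteeism and presenteeism costs. The article gives none of these amounts, so the effect on the ratio cannot be calculated.

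**The case against.** The other side has four fair points.

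- **The bias is conditional.** A reader might infer that the incremental cost is certainly biased, or that community services in this trial are known to be subsidised. The article supports neither. It states no funding arrangement and no expected difference in use. If participants pay the full cost, or if third-party-funded cost is equal between arms, the error is zero. This stands.
- **The multiples describe one component.** The 4-, 2- and 1.3-fold factors follow from assumed shares that are equal in both arms, and they say nothing about the whole ratio. Community services may be small beside lost productivity. This stands.
- **Only a secondary analysis is affected.** The health-sector ratio and the clinical outcomes do not use these costs. This stands.
- **The problem can be repaired at analysis.** Quantities are recorded, so full unit costs can be applied later. This makes the point less urgent, but the rule as written would still be the one applied.

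A reader might also infer that the rule favours the novel strategy, or that it undermines the Discussion's expectation of wider savings. Neither follows. With equal shares, if the novel arm used fewer such services, its saving would be understated. The Discussion sets the class-based programme against one-to-one outpatient care and does not rest its expectation on community-service use.

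None of these points reconciles an out-of-pocket rule with a societal perspective.

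**Conclusion.** The point holds as a mismatch between a stated valuation rule and a stated perspective, and it should be corrected. Any third-party share of community-service cost is missing from both economic analyses.

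Whether this biases the societal incremental cost depends on whether that share differs between arms. A difference is plausible, because early home exercise followed by later classes is compared with usual care that may be inpatient, but the article does not quantify it. With equal participant shares, the component shrinks towards zero by the fraction (1 − s). With unequal shares, the size and even the sign can change. The direction for the whole ratio cannot be determined from the article, and the effect may be small. The finding does not reach the primary economic result.

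**What to change.** Change the rule in both places, Health economic outcomes and Health economic analysis. In the societal analysis, value each community service as recorded quantity (type, hours or days) times a full unit cost that does not depend on who pays. Report participants' out-of-pocket payments separately as a participant-perspective item, and do not add them to the full cost, since that would count the same resource twice. The planned sensitivity analysis on cost weights can then cover the community-service unit costs as well.

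The cost is finding unit costs for a few service types. The diary already collects the quantities, so participants are asked for nothing new, and the primary analysis does not change.
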